#### Normal control group

Of the recruited healthy subjects, those with an average weakest link score minus 1 standard deviation will compose the group of individuals without cognitive vulnerability to depression, i.e., the normal control group. Individuals in the normal control group will be interviewed by two experienced psychiatrists using the SCID to exclude those suffering from depression and other axis I diseases. Ultimately, the control group will comprise 30 subjects, and the control group and the intervention and waiting subgroups of the group of individuals cognitively vulnerable to depression will be homogenous in terms of demographic variables and depression symptoms.

The inclusion criteria are described as follows: participants (a) with average CSQ weakest link score minus 1 standard deviation; (b) with Han ethnicity; (c) aged 18–25 years; (d) who are right-handed; (e) who have normal or corrected vision; (f) who are local community residents; (g) who can understand the content of the study, are willing to participate, and are committed to completing the entire experiment; and (h) who signed an informed consent form.

The exclusion criteria are described as follows: participants (a) who meet the diagnostic criteria for depression or other axis diseases; (b) history of taking any antidepressants or antipsychotics; (c) history of alcohol or drug abuse or dependence; (d) history of central nervous system diseases, e.g., head injury or epilepsy; (e) history of multiple sclerosis or major physical diseases; (f) history of electroshock therapy; (g) history of mental illness in first-degree relatives; and (h) contraindications to MRI.

Sample size calculation: An *a priori* power analysis found that a sample size of 75 participants per group (*N* = 150) would be sufficient with a medium effect size (Cohen’s d = 0.0.39) and 65% power (computed with G*power 3.1). These estimates were based on previous research examining changes in HRSD/BDI-II scores before and after CR training when compared to the waiting-list control condition (Berking et al., 2019). Since the sample size projection considered an anticipated 20% dropout rate, the target sample size was 188 patients.

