Randomization to treatment will be completed with a computer-generated list of random numbers, and each participant will be randomly assigned to either the intervention group or the control group with a 1:1 allocation and double-blinded. The randomization will minimize group differences in demographic factors and instrument scores (Pocock and Simon, 1975).

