### Statistical analysis

#### Behavioral and self-report data

##### Intervention effect analysis

A 3 (group: CR = cognitively vulnerable intervention subgroup; WC = cognitively vulnerable waiting-list control subgroup; NC = normal control group) × 3 (time point: T_0_ = pretraining, T_1_ = post-training, T_2_ = 6-month follow-up) mixed design will be adopted. Using the HLM analysis, as well as mediating/modulating effect analyses, we will investigate (1) hypothesis 1, whether the changes in negative cognitive biases and depressive symptoms across time 1 and time 2 differ significantly among groups and (2) hypothesis 2, whether the changes in negative cognitive bias (negative interpretation bias and/or negative rumination bias) pre- and post-training could predict depression symptoms at T_1_ and/or T_2_.

To test hypothesis 1, we will conduct an HLM analysis with time (0 = pretraining; 1 = post-training), group (0 = CR; 1 = WC; 2 = NC), and the interaction between time and group as predictor variables and the with CESD score as the outcome variable. To test hypothesis 2, we will conduct mediating/modulating effect analyses among CR ability (RIT) and tendency (ERQ), negative cognitive bias (NCPBQ), cognitive vulnerability (CSQ), and depressive symptoms (CESD) at T_1_ and/or T_2_. The HLM and mediating/modulating effect analyses will be conducted in SPSS (Statistical Product and Service Solutions) software version 22.0 (SPSS, Inc., Chicago, IL, United States) combined with the PROCESS Macro (Hayes, 2012).

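### The hypothesis 1 model leaves the CR–WC comparison unadjusted for baseline CESD and the balancing factors, which loses power and may make its interval too wide

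*Protocol article*

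**What the plan says.** The randomisation paragraph of the protocol article (under Subjects, at the end of the Normal control group section) describes a 1:1 allocation and adds: "The randomization will minimize group differences in demographic factors and instrument scores". It cites the minimisation method. The same paragraph also says "Randomization to treatment will be completed with a computer-generated list of random numbers". The balancing factors are not named one by one. The Normal control group section also expects the groups, including the intervention and waiting subgroups, to be alike in demographics and depressive symptoms.

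The Intervention effect analysis section sets out the model for hypothesis 1: "To test hypothesis 1, we will conduct an HLM analysis with time" (coded 0 before and 1 after training), with group (CR, WC, NC) "and the interaction between time and group as predictor variables and the with CESD score as the outcome variable". No demographic factor and no baseline score is a predictor. Pretraining CESD is present, but as the response at time 0.

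The sample size paragraph plans "a sample size of 75 participants per group", d = 0.39 (printed with a stray "0."), 65% power, and 188 participants after allowing for 20% dropout.

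**The concern.** When arms are balanced by design on variables that predict the outcome measure, the true sampling variance of the treatment contrast falls. A model that leaves those variables out still counts their variance in its standard error. The interval is then wider than the design warrants and the test is conservative. If allocation is a plain random list the standard error is correct, but the comparison is still less precise than an adjusted one using data collected anyway.

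Power is at stake, in a trial planned at only 65%. The article lists the predictors of its main model, so this is a stated choice and not just a detail left to a fuller document. The point concerns CR versus WC only, because NC is not randomised.

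**Working it through.** **Inputs.** From the article: 75 per arm, d = 0.39, 65% power, 20% dropout, N = 188, and the model terms. Assumed, because the article gives no values: two-sided alpha of 5%; equal CESD variance at T0 and T1; pre-post correlation ρ between 0.3 and 0.8; and a share R² of the variance of change, up to 30%, explained by the balancing factors.

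**1. The plan's own figure.** The noncentrality is 0.39 × √(75/2) = 2.388. Power is 66.6% by the normal approximation and 66.0% by the noncentral t, which agrees with the stated 65%. A one-sided test would give 77%, which does not match. Dropout: 150/0.8 = 187.5, so 188. The calculation reproduces.

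**2. What the time × group term compares.** With two time points it is the CR–WC difference in mean change. With unit variance at each time:
- variance of change: 2(1 − ρ)
- residual variance of T1 CESD given T0 CESD: 1 − ρ²
- standard error ratio, change score to baseline-adjusted: √[2(1 − ρ)/(1 − ρ²)] = √[2/(1 + ρ)]
- share of change variance explained by T0 CESD: (1 − ρ)/2

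If d = 0.39 is on the change scale, the starting power is 66% and adjustment gives:

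| ρ | share explained by T0 CESD | SE ratio | power, adjusted |
|---|---|---|---|
| 0.3 | 35% | 1.240 | 84% |
| 0.5 | 25% | 1.155 | 78% |
| 0.7 | 15% | 1.085 | 73% |
| 0.8 | 10% | 1.054 | 71% |

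**3. Other factors that predict change.** Entering them with a time interaction multiplies the standard error by √(1 − R²). For R² of 5, 10, 20 and 30%, power is 68, 71, 76 and 81%.

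**4. Behaviour under minimisation.** Simulation used 3,000 trials per scenario, 150 participants, biased-coin minimisation with probability 0.8, ρ = 0.5 and an effect of 0 or 0.39.
- *Demographics balanced, shifting the CESD level only.* The reported SE is 0.163 against a true 0.162–0.167. Type I error is 5.7%, and power is 66.2% with or without the factors. Adjusting for T0 CESD as well gives 76.8%.
- *Demographics balanced, predicting change.* The reported SE is 0.182 against a true 0.165, a ratio of 1.10. Type I error is 3.4%. Power is 58%, against 67% when the factors are allowed to affect change.
- *T0 CESD also balanced.* The reported SE is 0.163 against a true 0.151, a ratio of 1.08. Type I error is 3.2%. Power is 66%, against 77.5% with baseline adjustment. A separate simulation of this case put the excess at about 11% and the type I error at 2.7%. The limit under perfect balance is the ratio 1.155, with type I error 2 × [1 − Φ(1.96 × 1.155)] ≈ 2.4%.

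**5. Would main-effect covariates repair it?** In a random-intercept fit, adding a strong main-effect covariate left the time × group SE at 0.2228; only the SE of the group main effect fell, from 0.280 to 0.233. T0 CESD added as a covariate while also serving as the time-0 response left the estimate unchanged, but the random-intercept variance collapsed. Under simple randomisation (4,000 trials) the reported SE was then 0.149 against a true 0.165, and type I error rose from 5.2% to 8.1%. A second run gave 6.8%.

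**The case against.** Five points can be made for the plan.

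- *Baseline CESD is in the model.* True, as the time-0 outcome. A reader might infer that the model ignores every balanced score, and that goes too far. But being a response is not the same as being adjusted for: the contrast remains a difference in mean change, and the table above shows what that costs.
- *Time × group is a within-person contrast, so stable differences between people cancel.* This stands in full for factors that only shift the CESD level. It is therefore wrong to infer that every omitted factor widens the interval. The argument does not cover T0 CESD itself, or factors that predict change.
- *It is not settled that minimisation is used, or on which scores.* This stands. The text has both a random-number list and the minimisation citation. The reference to instrument scores, and the wish for groups alike in depressive symptoms, make T0 CESD a likely balancing variable but not a certain one. Under a plain list the stated interval is valid, and only the efficiency argument remains.
- *The correlation and R² are assumed.* They are, which is why ranges are shown. For balancing factors other than T0 CESD, the loss starts at zero.
- *Covariate lists usually sit in the full analysis plan.* That would excuse an article silent about the model. This one names the predictors, so the statement can be judged as it stands.

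**Conclusion.** The stated hypothesis 1 model does not adjust the randomised comparison for baseline CESD or for the factors that allocation is meant to balance. The cost depends on two unknowns.

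- If T0 CESD or factors that predict change are balanced by design, then at ρ = 0.5 the SE is about 8–11% too large and the type I error is about 3% instead of 5%.
- Under either form of allocation, baseline adjustment is more efficient: from about 66% power to 71–84% for ρ from 0.8 to 0.3. The SE ratio does not depend on the scale of d, but these power figures assume that d = 0.39 is on the change scale.

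A reader might infer that the main result would be biased or prone to false positives. The documents do not support that: any error in the stated model is in the conservative direction. The change is nevertheless worth making, because planned power is low and the remedy is cheap.

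**What to change.** For the randomised CR versus WC contrast only, report the effect from a model of post-training CESD on arm, adjusted for T0 CESD and the factors used to balance the arms. An equivalent choice is a longitudinal model with a common CR/WC mean at T0 and factor × time terms. Comparisons with NC can stay in a separate model.

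Do not add T0 CESD or the factors as main effects to the existing time × group model, for the reasons in step 5 of the working.

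The randomisation paragraph should also say whether a random list or minimisation is used and name the balancing factors, so that the covariate list can be written.

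The cost is one extra model statement and reliance on a linear baseline adjustment. All the values are collected at T0, so there is no added data collection and no change in sample size.

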On the other hand, the frequent user of CR showed stronger downregulation of amygdala activation to negative emotion stimuli (Kanske et al., 2012), and CR in healthy individuals can attenuate the excitatory connectivity from the dlPFC to the inferior frontal gyrus (IFG) and increase the inhibitory connectivity from the IFG to the dlPFC, which supports the selection of appropriate alternative CR strategies (reinterpretations) in the IFG, and afterward, inhibition of original interpretations maintained and monitored in the dlPFC (Morawetz et al., 2016). Neurofeedback-guided CR training targeting the left vlPFC improved the frequency of CR strategy use (indexed with ERQ) as well as depression symptoms (Keller et al., 2021). Therefore, CR training may enhance CR ability by changing the functional activity/connectivity pattern of prefrontal-amygdala circuits, which then alleviates cognitive biases and thus depressive symptoms.

Researchers suggested that specific measures using lab-based tasks may be more sensitive to detect training effects (Cohen and Ochsner, 2018). Therefore, in this study, we will combine the RIT, CR training, and fMRI, as well as self-report measures (cognitive/emotion/symptoms) to address the following aims: (1) to examine whether the CR ability (reappraisal inventiveness) of the population with cognitive vulnerability to depression is abnormal; (2) to test the hypothesis that CR training alleviates depressive symptoms through the mediators of cognitive bias (e.g., interpretation bias and/or rumination bias); (3) to investigate the neural substrates (structural/functional) of prefrontal–amygdala circuits through which CR training improves the ability to generate a CR strategy; and (4) to examine the short- and/or long-term effects of CR training on reducing depression symptoms in cognitively vulnerable individuals immediately after intervention and/or 6 months to provide theoretical and practical evidence for early intervention in these populations. We postulate that CR training improves CR ability (RIT) by changing the brain activity/function connectivity of the prefrontal-amygdala circuits, thereby reducing negative cognitive biases (NCPBQ-NIB, NCPBQ-NRB, and CSQ) and improving depression symptoms (CESD) (Figure 1).

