#### Short- and long-term antidepressant effects of cognitive reappraisal training on individuals cognitively vulnerable to depression

Through follow-up immediately after intervention or 6 months after the intervention, we will validate the hypothesis of the reduction in cognitive vulnerability to depression and depression symptoms through improvements in reappraisal inventiveness with CR training by constructing a hierarchical linear model (HLM) analysis and mediating/modulating effect analyses.

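### The hypothesis 1 model codes time as pre- and post-training only, which contradicts the three-time-point design and leaves the 6-month effect of aim 4 without a between-group estimate as written

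*Protocol article*

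**What the plan says.** All of this is in the protocol article.

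- **Design** (Intervention effect analysis). The design crosses three groups (training, CR; waiting list, WC; normal control, NC) with three assessments: "time point: T_0_ = pretraining, T_1_ = post-training, T_2_ = 6-month follow-up".
- **Hypothesis 1** (same section). It asks whether changes in negative cognitive biases and "depressive symptoms across time 1 and time 2 differ significantly among groups".
- **Model for hypothesis 1** (same section). It is specified as an "HLM analysis with time (0 = pretraining; 1 = post-training"), with group and time-by-group as the other predictors. CESD is the single outcome.
- **Hypothesis 2** (same section). It asks whether changes in bias "could predict depression symptoms at T_1_ and/or T_2". This is a question of prediction and mediation.
- **Aim 4** (Introduction). The aim is "to examine the short- and/or long-term effects of CR training on reducing depression symptoms in cognitively vulnerable individuals". The Abstract states the same aim but joins the two time points with *and*.
- **Procedure**, short- and long-term effects. "Through follow-up immediately after intervention or 6 months after the intervention, we will validate the hypothesis", and an HLM is named there as one of the tools. No time coding is given.
- **Primary outcome.** CESD is listed without a time point.

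**The concern.** The Intervention effect analysis section sets out a design with a 6-month assessment and then specifies a model that cannot use it. The 6-month effect is a headline objective: it appears in the Abstract, in the Introduction and under its own Procedure heading. If the analyst follows the written model, 6-month CESD data are collected but no estimate of training against waiting list comes from them. If T2 is added later without a prior statement, its place in the analysis (primary, secondary or exploratory) will have been chosen after the data could be seen.

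Two smaller mismatches sit beside this one. The model has no bias outcome, although hypothesis 1 names the biases. And the aim is worded three ways (*and*, *and/or*, *or*), so the document does not settle which time point carries the claim about CESD.

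**Working it through.** **1. What the written model can estimate.** Take group as categorical with CR as reference. Let W and N be indicators for waiting list and normal control, and let t = 0 or 1 as coded:

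E[CESD] = b0 + b1·t + b2·W + b3·N + b4·t·W + b5·t·N

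- Mean change in CR: (b0 + b1) − b0 = b1.
- Mean change in WC: (b0 + b1 + b2 + b4) − (b0 + b2) = b1 + b4.
- CR minus WC in change: b1 − (b1 + b4) = −b4.

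So there is one CR-versus-WC contrast, and it is T1 minus T0. The model has 6 mean parameters for 3 × 2 = 6 cells. The stated design has 3 × 3 = 9 cells. The 9 − 6 = 3 cells without a parameter are T2 in each group.

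**2. What a three-level time factor gives.** With p = 1 at T1 and f = 1 at T2:

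E[CESD] = c0 + c1·p + c2·f + c3·W + c4·N + c5·p·W + c6·f·W + c7·p·N + c8·f·N

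This has 9 parameters for 9 cells. CR minus WC in change from T0 is −c5 at T1 and −c6 at T2. The second of these is what the long-term part of aim 4 needs.

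**3. Does the wording of hypothesis 1 rescue the model?** The phrase *time 1 and time 2* has two readings.

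- If it means T1 and T2, the model contradicts it, because the model has T0 and T1 and no T2.
- If it means the first and second assessments (T0 and T1), it agrees with the model, but then no stated hypothesis covers the between-group 6-month effect.

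The mismatch survives either reading.

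**4. Is T2 CESD compared between groups in another specified analysis?** In hypothesis 2, and in the imaging sections on brain volume, regional activation and functional connectivity, T2 depressive symptoms are something to be predicted. The between-group *t*-tests in the connectivity section concern connectivity. None of these is a randomised comparison of CESD at 6 months. The Procedure section does name an HLM for follow-up, but without coding.

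**5. Outcomes.** Hypothesis 1 names two kinds of outcome, negative cognitive biases and depressive symptoms. The model for it names one, CESD.

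**6. Sample size.** The article states 75 per group, a standardised difference printed as 0.0.39 (read here as 0.39), 65% power, and 188 after 20% dropout. With two-sided 5% assumed, since no level is stated, a two-sample *t*-test gives 66% power. Dropout: 150 / 0.80 = 187.5, rounded up to 188. Both figures reproduce, so the problem lies in the model wording and not in these numbers.

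**The case against.** The strongest reply is that the 6-month comparison is plainly intended. T2 is a level of the design under the heading on intervention effects, and the Procedure section names an HLM for the 6-month follow-up. The 0/1 line may be a drafting slip or a condensed description. This stands as far as it goes: the documents do not support saying that the groups are never to be compared at 6 months. What remains is that the one model written out in detail conflicts with the design around it, and the other mention of an HLM gives no coding to resolve the conflict.

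A reader might also infer from the *and/or* wording that the trial gives itself two unadjusted chances of success. The documents do not support that either.

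- No success rule is stated.
- In the analysis section the *and/or* on time points belongs to hypothesis 2. The Limitations section calls its bias measures exploratory.
- For the treatment effect the phrase occurs in a statement of aims, which the Abstract words with *and*.
- A multiplicity rule may sit in an analysis plan that is not shown.
- The model as coded yields a single time contrast, so it offers no second chance. Any familywise error figure would describe a rule the authors have not written.

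It can further be said that the bias measures are secondary and that a short article need not repeat a model for each. That lowers the weight of the outcome mismatch, but hypothesis 1 still names outcomes that its own model leaves out.

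**Conclusion.** The point holds as an internal contradiction. The design has three time points and aim 4 asks about 6 months, but the specified hypothesis 1 model stops at post-training and so gives no between-group CESD estimate at T2. Its size is structural: one of the two CR-versus-WC contrasts that the aim requires cannot be obtained from the written model. The missing bias outcome is a lesser mismatch in the same sentence, and the varying conjunction in aim 4 is a matter of consistency.

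The conclusion rests on reading the 0/1 coding literally and group as categorical. If group were entered as a number there would still be no T2 term. It does not rest on any assumed significance level or correlation. One limit applies to the repaired analysis: the text shown does not say whether the waiting-list group remains untrained until T2, and the meaning of a T2 contrast depends on that.

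**What to change.** 1. In the hypothesis 1 HLM, code time as a three-level categorical factor (T0, T1, T2), with group categorical.
2. State the CR-minus-WC CESD contrast at T1 and at T2.
3. Name one primary time point, or a fixed testing order such as T1 then T2. Then word aim 4 to match in the Abstract, the Introduction and the Procedure section, and replace *time 1 and time 2* in hypothesis 1 with the T labels.
4. Run the same model for the NCPBQ bias scores as secondary or exploratory outcomes, in line with the Limitations section.

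**Cost.** This is analysis wording only, with no new data. According to the Ethics statement nobody had been recruited at submission, so on that account the change could precede any data. A fixed order needs no split of the significance level and no extra participants. Its price is that an effect seen only at the later-tested time point could not be claimed as confirmatory. For comparison, if the authors preferred to test each time point at 2.5%, power per time point at 75 per group and 0.39 would fall from 66% to 55%. Holding 65% would then take 92 per group: 2 × 92 = 184, and 184 / 0.80 = 230 with dropout.

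### The CR versus waiting-list effect on CESD is tested as a difference in change, which is unbiased but usually less precise than adjusting for the baseline CESD already collected

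*Protocol article*

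**What the plan says.** The Intervention effect analysis section of the protocol article asks "whether the changes in negative cognitive biases and depressive symptoms across time 1 and time 2 differ significantly among groups". The model for this question has three predictors. Two are main effects, coded as "time (0 = pretraining; 1 = post-training), group (0 = CR; 1 = WC; 2 = NC"). The third predictor and the response are given as "and the interaction between time and group as predictor variables and the with CESD score as the outcome variable". That fixes the outcome, the time points and the full list of predictors. It mentions neither baseline CESD as a covariate nor a common baseline mean for the two vulnerable subgroups.

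The randomisation paragraph at the end of the Normal control group section says that "each participant will be randomly assigned to either the intervention group or the control group with a 1:1 allocation" and that "The randomization will minimize group differences in demographic factors and instrument scores". The normal controls are not randomised. They are selected from the low end of the CSQ weakest-link score, and "Ultimately, the control group will comprise 30 subjects".

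The sample size paragraph in the same section gives "a sample size of 75 participants per group" (N = 150) for a d printed as 0.0.39, "and 65% power (computed with G*power 3.1"). It bases d on changes in HRSD/BDI-II scores against a waiting list, and does not say whether d is scaled by the SD of the score or the SD of the change.

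**The concern.** CESD at T0 and at T1 is the response in the same model, so the group term estimates a separate T0 mean for each arm. The CR versus WC interaction is then the difference between arms in mean T0-to-T1 change.

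For randomised arms the true T0 difference is zero in expectation. Estimating it freely, and subtracting it in full from the T1 difference, carries the chance imbalance and measurement noise of T0 into the treatment effect. An analysis that uses T0 CESD as a covariate, or that constrains the two arms to one T0 mean, subtracts only the part of the T0 difference that predicts T1.

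Precision is at stake, not validity. It matters here because the design plans only 65% power, so there is little to spare.

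**Working it through.** **Inputs.** n = 75 per arm, d = 0.39 (reading 0.0.39 as a misprint) and 65% power come from the sample size paragraph. Assumed, because the document is silent: two-sided alpha of 5%, and a T0–T1 correlation r of CESD between 0.3 and 0.7. SD0 and SD1 are the CESD SDs at T0 and T1.

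**1. The plan's own figure.** A two-sample comparison with 75 per arm and d = 0.39, by noncentral t, gives 66.0% power (66.6% by the normal approximation). The normal formula needs 73 per arm for 65%. A one-sided test gives 77%, which does not fit. The stated design is therefore reproduced with a two-sided 5% test. For dropout, 150 / 0.80 = 187.5, i.e. the stated 188.

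**2. The planned interaction is a change-score contrast.** One simulated data set with 75, 75 and 30 subjects, fitted by a random-intercept model with time, group as a factor and their interaction, gave a CR–WC interaction of −0.301. The difference in mean changes was −0.509 − (−0.208) = −0.301.

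**3. Variances (per subject).**
- Change score: SD0² + SD1² − 2·r·SD0·SD1.
- Baseline-adjusted: SD1²·(1 − r²).
- Difference: SD0² − 2·r·SD0·SD1 + r²·SD1² = (SD0 − r·SD1)².

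The excess is never negative, and is zero only when r = SD0/SD1. With equal SDs the ratio of adjusted to change-score variance is (1 − r²) / [2(1 − r)] = (1 + r)/2, i.e. 0.65, 0.75 and 0.85 at r = 0.3, 0.5 and 0.7.

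**4. Power if d = 0.39 is in score SDs (equal SDs, noncentral t).** The effective d is 0.39/√[2(1 − r)] as planned and 0.39/√(1 − r²) adjusted.

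| r | d planned | d adjusted | Power planned | Power adjusted |
|---|---|---|---|---|
| 0.3 | 0.330 | 0.409 | 52% | 70% |
| 0.5 | 0.390 | 0.450 | 66% | 78% |
| 0.7 | 0.503 | 0.546 | 87% | 91% |

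A simulation of 4,000 trials per row gave 52% v 71%, 67% v 79% and 86% v 91%.

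**5. Power if d = 0.39 is in change SDs (equal SDs).** The planned test has 66% at every r. The adjusted effective d is 0.39/√[(1 + r)/2], i.e. 0.484, 0.450 and 0.423, which gives 84%, 78% and 73%.

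**6. Unequal SDs.** Take SD0 = 1 and SD1 = 1.25 as an illustration.
- r = 0.5: change 1 + 1.5625 − 1.25 = 1.3125; adjusted 1.5625 × 0.75 = 1.1719; ratio 0.89.
- r = 0.7: change 1 + 1.5625 − 1.75 = 0.8125; adjusted 1.5625 × 0.51 = 0.7969; ratio 0.98.

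The gain falls from 33% to 12% in equivalent sample size at r = 0.5 (1/0.75 against 1/0.89), and from 18% to 2% at r = 0.7 (1/0.85 against 1/0.98).

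**The case against.** The strongest reply is that nothing in the document is wrong. The interaction is a valid, unbiased test under randomisation, and it matches the stated question about changes. An article may also leave covariates to a fuller plan. The first part stands: a reader might infer that the planned test is biased or invalid, and the documents do not support that. The last part does not remove the point, because the section lists the predictors of this model. The choice is stated rather than left open.

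A second reply is that the size is uncertain, and this also stands. The document gives no r, SD, alpha or sidedness. Two stronger readings are tempting:
- *The planned model loses precision at every correlation below 1.* This is true only with equal SDs at T0 and T1. If SD1 exceeds SD0, the loss vanishes at r = SD0/SD1.
- *The planned test misses its own 65%.* This needs d in score SDs and r below about 0.5. The sample size paragraph speaks of changes in scores, so d may be in change SDs, and then there is no shortfall.

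A third reply is that balancing instrument scores at allocation already removes the T0 difference. CESD is not named among those scores. Even perfect balance would not rescue the test, because the model's standard error would still include T0 variance. At r = 0.5 with equal SDs, the true variance is 0.75 of what the model assumes. The critical value is then effectively 1.96/√0.75 = 2.26, an actual error near 2.4%. In score SDs the standardised effect is 0.39/√(2 × 0.75/75) = 2.76, so power is about 69%, against 78% adjusted.

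**Conclusion.** The point holds as a matter of efficiency. The stated model gives an unbiased CR versus waiting-list effect on CESD. In large samples it is never more precise than a baseline-adjusted analysis, and usually less so, with excess variance proportional to (SD0 − r·SD1)².

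With equal SDs, 75 per arm and two-sided 5%, the gain from adjustment over r = 0.3 to 0.7 is about 18 to 5 percentage points of power if d is in score SDs, and about 18 to 7 if d is in change SDs. It can be close to nil if the spread of CESD grows after training and r is high. The direction is secure; the size is a range because the document supplies neither r nor the SDs. The change is worth making in a trial planned at 65% power, but the planned analysis is not invalid without it.

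**What to change.** In the Intervention effect analysis section, reword the hypothesis 1 model for the randomised comparison in one of two ways:
- Keep the mixed model, but constrain CR and WC to a common T0 CESD mean: retain time and the group-by-time terms, and drop the CR–WC difference at T0. The normal controls were selected on a different CSQ range and must keep their own T0 mean.
- Alternatively, analyse T1 (and T2) CESD for CR versus WC with T0 CESD as a covariate.

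The two agree closely, but not exactly when data are missing, and 20% dropout is expected. So name one in advance and report it as the training effect. The cost is a change of wording, with no new data, visits or participants. The Ethics statement says that nobody had been recruited at submission, so at that stage the change could be made free of any suspicion that it was driven by data.
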